#### For participants without previous meditation practice

- French mother tongue;
- Available for the trial duration (24 months);
- Retired since 1 year or more;
- No preference regarding the intervention group;
- Not having regularly or intensively practiced meditation or comparable practices (yoga, Qi Gong, Alexander technique)
  - more than one day per week for more than six months consecutively over the last 10 years,
  - intensively (internship or retreat > five consecutive days) over the past 10 years,
  - more than 25 days of retreats (cumulatively) prior to the last 10 years;
- Not speaking English fluently.

#### For expert meditators

- Formal meditation practice > 10 000 hours in the whole life, including at least 6 cumulated months of retreat;
- Daily meditation practice (at least 6 days/week, 45 minutes/day);
- Mindfulness meditation practice (i.e. mindfulness, Samatha/ Vipassana, Zazen (Zen), Shikantaza (Zen), focused attention, Mahamudra/ Dzogchen), and compassion mediation practice (i.e. tonglen, metta / karuna, meditation on Bodhichitta).

### Exclusion criteria

- Contraindication to MRI or PET Amyvid® or Glucotep®;
- For security reasons related with the use of Amyvid® and Glucotep®, a blood sampling allowing to measure hepatic and renal functions will be performed at the V1 visit and V4 (after 18 months) before the PET scan. In particular, the glomerular filtration rate will be calculated from the results obtained. In case of kidney failure, hepatic failure, diabetes (glycaemia > 1.6 g/L) or any other biological anomalies of grade 3 or higher severity detected, the PET scan will not be performed.
- Hypersensitivity to Amyvid® or to Glucotep®;
- Presence of a major neurological or psychiatric disorder (including an addiction to alcohol or drugs);
- History of cerebral disease (vascular, degenerative, physical malformation, tumor, or head trauma with loss of consciousness for more than an hour);
- Presence of a chronic disease or acute unstable illness (respiratory, cardiovascular, digestive, renal, metabolic, hematologic, endocrine or infectious);
- Current or recent medication that may interfere with cognitive action or radiological measures (psychotropic drugs, antihistamines acting anticholinergic, anti-Parkinsonian drugs, benzodiazepines, non-steroidal anti-inflammatory agents, antiepileptic, central analgesic and muscle relaxants agents);
- Under legal guardianship or incapacitation;
- Inclusion in another biomedical research protocol at baseline, if including use of a radiolabel for radiological measures;

- Physical or behavioral inabilities to perform the follow-up visits as planned in the study protocol.

## Sample size

### **For the randomized clinical trial with non-expert seniors:**

The comparison of the meditation vs. no intervention arms will focus on the change in 1) volume and 2) metabolism of the anterior cingulate cortex from baseline to the end of the 18-months intervention, with an expected effect size of 0.75.

We expect the same effect size of 0.75 for the comparison between the meditation arm and learning of English arm on the change in 1) volume and 2) metabolism of the insula from baseline to the end of the 18-months intervention.

To demonstrate an effect size of 0.75 for each of the four comparisons, with 80% power and a two-sided type I error of 1.25% (Bonferroni correction for test multiplicity), 42 participants per arm need to be included for a total of 126 participants.

In order to increase the statistical power of the secondary analysis on the PET-FDG examination carried out starting from the second wave of inclusion, 24 additional participants will be recruited (additional 8 participants per group) for a total of 150 participants.

### **Experienced meditators:**

For recruitment capacity reasons, it is possible to recruit 30 experienced meditators in the study. With the inclusion of 30 experienced meditators and 126 non-expert seniors, our power to highlight an effect size of 0.74 in the comparison of brain imaging data with a significance level of 5%, is 95%.

## Outcomes

### **Primary outcomes**

For the comparison between meditation intervention and no intervention (**OBJECTIVE 1**):

- Change in anterior cingulate cortex volume (T1-weighted MRI) from baseline to 18 months;
- Change in anterior cingulate cortex perfusion (early PET-Amyvid® scan) from baseline to 18 months).

For the comparison between meditation intervention and language learning intervention (**OBJECTIVE 1BIS**):

- Change in insula volume (T1-weighted MRI) from baseline to 18 months;
- Change in insula perfusion (early PET-Amyvid® scan) from baseline to 18 months).

### **Secondary outcomes**

#### **Behavioral outcomes (OBJECTIVES 2, 4, 6, 7 and 9):**

The main behavioural outcome will correspond to the comparison between meditation intervention and language learning intervention on the global metacognitive composite score, consisting in the mean of the attentional, constructive and deconstructive subscores as defined in (Dahl et al., 2015) and updated in (Schlosser et al., Submitted); see Section “*Analysis of trial objectives*” below for further details about this score.

Additional composite scores will be computed as z-scores measured from the neuropsychological tests and/or the questionnaires. Composite scores will correspond to the mean of z-scores calculated from all the cognitive scores obtained for the corresponding cognitive function that will have a normal distribution and will not have floor or ceiling effect. Additional exploratory analyses will be conducted on all individual behavioural measures obtained.

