### 5.2. Secondary evaluation criteria

- Behavioural measurements (OBJECTIVES 2, 4, 6, 7, 9) :

a composite score per function assessed by the neuropsychological tests and questionnaires (listed in Tables 5 and 6 below, see section 6.7). The composite scores will be an average of z-scores calculated from all scores collected for the corresponding function that have a normal distribution and do not show a floor/ceiling effect. (In addition, exploratory analyses will be conducted on all individual behavioural measurements collected).
- Imaging measurements (OBJECTIVES 2, 4, 6, 7, 8, 9):
  - Volume of gray matter in each brain voxel;
  - Volume of the hippocampus and hippocampal subfields;
  - Brain perfusion measure in each brain voxel;
  - Fractional anisotropy and mean diffusivity in each brain voxel;
  - Number, size and location of white matter lesions;
  - Magnetic susceptibility measured in each brain voxel;
  - Functional brain connectivity in a non-meditative state;
  - Beta-amyloid load (from the radiopharmaceutical Amyvid® ) measured in each brain voxel and global average in the gray matter;
  - Cerebral glucose consumption at rest (relative to the average consumption measured in the cerebellum)
  - Brain activity measured in fMRI specifically associated with emotional processing (comparing emotional and neutral items) from the Rest-SoVT task.
  - Brain activity associated with attentional processus of alertness, inhibition and sustained attention measured in fMRI during the AX-CPT task.
  - Spontaneous oscillatory activity (EEG) in a resting state.
  - EEG brain activity specifically associated with the processing of auditory stimuli (MMN protocol).
- Sleep measurements (OBJECTIVES 2, 4, 6, 7, 9):
  - Subjective sleep measurements collected by sleep questionnaires (Tables 6 and 7 below)
  - Actimetry parameters (average sleep duration, fragmentation index of activity and rest periods, regularity of activity/rest cycle).
  - Data collected through polysomnographic recordings
  - Data collected with the Somno-Art device.
- Biological measurements (OBJECTIVES 2, 4, 6, 7, 9):
  - Blood measurements as listed in Table 8 below, see section 7.3. 4 (such as total cholesterol, BNP, bioavailable testosterone, serotonin, estradiol, SHBG, SDHEA, cytokines, cortisol,

- telomere length, telomerase activity, A $\beta$  1-42, Tau/phosphoTau proteins, tPA and BDNF, fibrinogen and GFAP)

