### 1.7.2 Secondary outcomes

#### **Behavioral outcomes (OBJECTIVES 2, 4, 6 et 7) :**

One composite score per cognitive area assessed by the neuropsychological tests and the questionnaires. The composite scores will correspond to the mean of z-scores calculated from all the cognitive scores obtained for the corresponding cognitive function that will have a normal distribution and will not have floor or ceiling effect. (Additional exploratory analyses will be conducted on all individual behavioural measures obtained).

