## Comparative/Correlational analysis

Qualitative variables will be compared between the groups with the  $\chi^2$  test or the corrected  $\chi^2$  or non-parametric Fisher's exact test, according to the values of expected frequency under the independence assumption. A logistic or polytomic model will be used to consider adjustments if necessary. The assumption of log-linearity of the association will be systematically checked.

Quantitative variables will be compared between 2 groups of intervention by Student t test if the conditions of validity are respected (normal distribution, homogeneous variances). If the variances are unequal between the 2 groups, a t-test for unequal variances will be used, if the distribution is not normal, a non-parametric Wilcoxon test will be used.

Quantitative variables will be compared between 3 groups of intervention with analysis of variance (ANOVA) if the conditions of validity are respected (normal distribution, homogeneous variances). If the distribution is not normal, a non-parametric Kruskal-Wallis test will be used.

Covariates will be added to the model, or linear regression model will be used to adjust on variables, if necessary. The assumption of linearity of the association will be systematically checked. The other assumptions of the model (normality and homoscedasticity of residuals) will be studied. A transformation of the quantitative variable may be considered if necessary.

Multiple regression models, general linear models and/or independent component analyses, principal component analyses or confirmatory factor analyses would be performed to assess the relationships between variables and/or to extract components from multiple variables,

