#### Secondary objectives

##### *Objective 2 (WP 1 to 6)*

For the main secondary outcome, the difference between the inclusion and 18 months of i) the global metacognitive composite score, and ii) the attentional, constructive and deconstructive subscores, will be compared between the meditation intervention and language learning intervention groups.

These scores will be computed as described in (Schlosser et al., Submitted). Briefly, the metacognitive composite score drew from the following self-report measures employed in the Age-Well randomised controlled trial (See Poisnel et al. for details and corresponding references): the Compassionate Love Scale (CLS; stranger-humanity version), the Drexel Defusion Scale (DDS), the Five Facet Mindfulness Questionnaire (FFMQ), the Interpersonal Reactivity Index (IRI), the Multidimensional Assessment of Interoceptive Awareness Version 2 (MAIA-2), and the Prosocialness Scale. Amongst those, seven subscales were judged to primarily capture attentional aspects: noticing (MAIA subscale), attention regulation (MAIA), emotional awareness (MAIA), self-regulation (MAIA), body listening (MAIA), observing (FFMQ), and acting with awareness (FFMQ). Four (sub)scales were judged to primarily capture constructive aspects: the CLS, empathic concern (IRI subscale), perspective taking (IRI), and the Prosocialness Scale. Another four scales were judged to primarily capture deconstructive aspects: the DDS, non-judging (FFMQ), non-reactivity (FFMQ), distress (IRI).

To compute each composite score, scale scores will be first standardised using their baseline mean and standard deviation, and the sum of the standardised scale scores will then be divided by the number of scales included in the respective composite. Scales will be reverse-scored if higher total scores reflect worse functioning. Ergo, higher composite scores will indicate higher capacities in the psychological processes characterising the three meditation families. Participants with missing scale scores will not be included in the composite score to which this scale is assigned.

The evolution of the same scores in the passive control group will be provided for the sake of description. Moreover, the difference between the inclusion and 18 months of all additional composite scores and individual behavioural cognitive, psychoaffectives, life, blood, sleep and imaging measures will be compared between

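### The additional behavioural composites keep only scores that turn out normal and free of floor or ceiling effects, by an undefined screen, so their content depends on the data and is not fixed in advance

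*Combined protocol and SAP*

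**What the plan says.** Protocol section 5.2 (Secondary evaluation criteria) makes the behavioural criterion one composite per function, an average of z-scores "calculated from all scores collected for the corresponding function that have a normal distribution and do not show a floor/ceiling effect". Section 1.7.2 of the primary SAP repeats the condition for scores "that will have a normal distribution and will not have floor or ceiling effect". The secondary SAP (Behavioral outcomes, Objectives 2, 4, 6, 7 and 9) states: "Additional composite scores will be computed as z-scores measured from the neuropsychological tests and/or the questionnaires". It then limits each to scores "for the corresponding cognitive function that will have a normal distribution and will not have floor or ceiling effect". Its filter sentence speaks of cognitive scores, but the sentence before it and protocol 5.2 cover questionnaires as well.

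Three other provisions bear on this.

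- **Transformation.** The Comparative/Correlational analysis section of the secondary SAP says "A transformation of the quantitative variable may be considered if necessary", and protocol 11.3.6 has a similar clause. Both concern the variable being analysed. Neither says that components are transformed before they are screened.
- **The metacognitive score.** Under Objective 2 the secondary SAP names this composite's scales in advance (for example, "seven subscales were judged to primarily capture attentional aspects"), and "scale scores will be first standardised using their baseline mean and standard deviation". It has no normality filter.
- **Timing.** The Purpose section of the secondary SAP requires approval before any analysis and before database freeze.

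**The concern.** This is a stated selection rule, not merely a missing detail, and it selects on observed distributions. Two analysts who follow the plan faithfully could build different composites under the same name. The scope for this is wide:

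- Most tests in protocol Table 5 yield several scores.
- Six work packages share the secondary analyses.
- Objective 4 includes the expert meditators and Objective 2 does not, so the pool on which a distribution is judged can change.
- Objective 2 plans mixed models over baseline, 9 and 18 months, but D2R and both digit spans are not given at 9 months (V2).

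The filter is also unnecessary. Normality matters, at most, for the analysed composite or its residuals, not for each component. Skewed times can be transformed and kept, and short integer scales can be averaged as they are. At stake are the prespecification and comparability of the additional cognitive and psycho-affective composites and, under some conditions, their power.

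**Working it through.** **1. The nearest stated figure.** The documents give no effect size, SD or power for any behavioural composite. The nearest figure is 42 per arm for the imaging comparisons (effect size 0.75, 80% power, two-sided 1.25%). The noncentral t solution is 41.24 per arm, which rounds up to 42, with 80.9% power at 42. The figure reproduces, so the plan's basic arithmetic is not in question.

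**2. How many scores would a screen remove?** The screens and distributions are assumptions; the sample size is the planned 150 non-expert seniors. Simulated share of samples in which a score is excluded (2,000 samples each):

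| Score | Shapiro-Wilk, p < 0.05 | Absolute skewness > 1 |
|---|---|---|
| Truly normal | 6% | 0% |
| Lognormal time, log-SD 0.2 | 72% | 5% |
| Lognormal time, log-SD 0.3 | 96% | 30% |
| Lognormal time, log-SD 0.4 | > 99% | 68% |
| Integer score, SD 2 | about 100% | 0% |
| Integer score, SD 5 | 11% | 0% |
| Log of the log-SD 0.4 time | 5% | 0% |

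The choice of screen, which the plan leaves open, decides the answer. A log transform removes the problem for times.

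**3. How stable is the content?** Take seven independent, mildly skewed tests (log-SD 0.05 to 0.2) and a Shapiro-Wilk screen at 5%. Two samples of 150 from the same population then select the same set only about 3% of the time. With seven essentially normal tests the figure is about 52%. Independence between tests is an assumption.

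**4. What would a smaller composite cost?** Table 5 lists seven attention/executive tests: Flanker, Stroop, digit symbol, Trail Making, D2R, and digit span forward and backward. For k equally weighted tests with common effect d and correlation ρ, the composite effect is d × √(k / (1 + (k − 1)ρ)). Power with n per arm is approximately Φ(composite effect × √(n/2) − 1.96). With d = 0.3 (assumed) and n = 50, √(n/2) = 5.

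Example at ρ = 0.2:
- k = 7: 0.3 × √(7/2.2) = 0.535; Φ(2.675 − 1.96) = 76%.
- k = 3: 0.3 × √(3/1.4) = 0.439; Φ(2.195 − 1.96) = 59%.

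| ρ | 7 tests | 3 tests | Loss (points) |
|---|---|---|---|
| 0.2 | 76% | 59% | 17 |
| 0.3 | 66% | 54% | 12 |
| 0.5 | 51% | 45% | 6 |
| 0.7 | 41% | 39% | 2 |

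**5. When the dropped tests respond less.** Give the four dropped tests d = 0.1, with ρ = 0.3. Keeping all seven gives a composite effect of ((3 × 0.3 + 4 × 0.1)/7) / √(2.8/7) = 0.294 and 31% power. Keeping three gives 0.411 and 54%. Break-even is an effect in the dropped tests of about 0.23 (ρ = 0.3) to 0.26 (ρ = 0.5), against 0.30 in those kept.

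**The case against.** The strongest reply is that little of consequence hangs on this rule. The secondary SAP makes the metacognitive composite the main behavioural outcome, and that score has a fixed list. The affected composites are additional ones, each tested at 5% with no power claim. Every individual measure is still analysed and compared between groups, so no score is lost to the trial. All of this stands and limits the weight of the point.

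Three stronger readings are tempting, and the documents do not support them.

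- **That most timed and short-range tests will be thrown out.** This holds under a strict Shapiro-Wilk screen, but the documents name that test only for the Lockdown sub-study, where transformation follows it. The rule also acts on scores, not tests: a test with several scores can lose one and stay in through another.
- **That power falls.** Step 5 shows that the sign depends on how responsive the excluded scores are. A score with a true floor or ceiling may well be among the less responsive.
- **That the intervention's own effect shapes the endpoint.** Nothing says that the screen uses 18-month or by-arm data, and protocol 3.2 keeps allocation hidden from those who analyse the data. Equally, nothing rules out 18-month data. Blinding would not fully answer that, because pooled 18-month distributions already carry any treatment effect. It remains an open possibility, not a finding.

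The transformation clauses do not rescue the rule, since neither is tied to component selection. Nor does approving the SAP before database freeze: what is approved is a filter whose result is not yet known.

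**Conclusion.** The point holds in a limited form. The filter is in the current text of all three places, has no operational definition, and makes the content of the additional behavioural composites depend on observed data. It is also unnecessary for an average of z-scores. It does not reach the primary imaging outcomes, the metacognitive composite or the Lockdown sub-study composites, for which no such filter is stated.

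That conclusion rests on the documents alone. The size of any harm rests on assumptions that they do not supply: the screening test, the score distributions, a per-test effect of 0.3 and the correlations. On those, exclusion of a moderately skewed time ranges from about 5% to over 99% of samples. The power change from losing four of seven tests runs from a loss of 17 points to a clear gain. It should be corrected as a matter of prespecification, with loss of scores and power described only as possible.

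**What to change.** In protocol 5.2, primary SAP 1.7.2 and the Behavioral outcomes section of the secondary SAP, replace the filter with these rules:

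- **Fixed list.** Name the component scores for each function from Tables 5 and 6, before unblinding.
- **Transform, do not exclude.** Keep skewed scores after a prespecified transformation: log for times; any rank-based or other mapping estimated once on pooled V1 data and applied unchanged later. Rank scores recomputed at each visit would erase mean change.
- **Floor or ceiling.** Drop a score only by a stated threshold, judged once on pooled V1 data of the non-expert seniors. These data precede randomization.
- **Scaling.** Standardise on the V1 mean and SD, signed so that higher is better.
- **Visits.** Use the full list for change from V1 to V3 (and V4). For the mixed models that use the 9-month data, use a separate fixed list of tests given at V1, V2 and V3; for attention/executive function that leaves four of the seven tests.
- **No baseline.** Leave tests without a V1 measure in non-experts (Cyberball and Empathic Dictator, by the footnote to Table 5) out of change composites.

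The cost is SAP wording and one table, with no new data. Composites with transformed components are slightly less direct to describe.

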#### **Radiological outcomes (OBJECTIVES 2, 4, 6, 7 and 8):**

- Grey and white matter volume in all brain voxels;
- hippocampal and hippocampal subfield volumes;
- Brain perfusion in all brain voxels;
- Fractional anisotropy and mean diffusivity in all brain voxels;
- number, size, type and location of white matter lesions;
- magnetic susceptibility index in all brain voxels;
- brain functional connectivity measures in all brain voxels at rest in a non-meditative state ;
- Brain amyloid load (of the PET-Amyvid® radiotracer) measured in all brain voxels as well as in a global grey matter mask;

- Brain activity measured with fMRI specifically associated with emotional processes (comparing emotional to neutral items) during the Rest-SoVT task.
- Brain activity measured with fMRI specifically associated with attentional processes (alertness, inhibition, sustained attention) during the AX-CPT task.

**Sleep-related outcomes (OBJECTIVES 2, 4, 6, 7 and 9):**

- Subjective measures of sleep collected via sleep questionnaires
- Data collected by actimetrics record (mean duration of sleep, fragmentation indices during activity and resting states, regularity of the rest-activity cycle).
- Data collected during polysomnographic sleep record: Total sleep time, Sleep onset latency, Sleep efficiency, % of Stage N1, % of Stage N2, % of Stage N3, % of Stage REM sleep, Wake After Sleep Onset (WASO), Apnea-hypopnea index (/TST), Arousal index

**Biological outcomes (OBJECTIVES 2, 4, 6 and 7):**

- Total cholesterol, Triglycerides, HDL-cholesterol, LDL-cholesterol, urea, creatinine, gamma glutamyl transferase, glutamate-oxaloacetate transaminase and glutamate-pyruvate transaminase, complete blood count, glycemia, insulin, high-sensitivity CRP, Cytokines, insulin-like growth factor-1, Peroxyredoxin, Brain Natriuretic Protein, Estradiol, Dehydroepiandrosterone-Sulfate, Cortisol, Sex Hormone Binding Globulin, bioavailable testosterone, Thyroid Stimulating Hormone, serotonin, tissue plasminogen activator, PAI 1, Brain-Derived Neurotrophic Factor, Tau and PhosphoTau, A $\beta$  40 & 42, NFL, lymphocytic immunotyping, telomeres and telomerase, ApoE4, cDNA/mRNA REST, GWAS,.

